### Study design

This RCT will be undertaken at two sites: Beijing Traditional Chinese Medicine Hospital Affiliated with Capital Medical University and Peking University People’s Hospital. In this study, we will compare the efficacy of Methycobal with or without acupuncture treatment in ISSNHL patients with flat or high-frequency drop audiograms (Figs. 1 and 2). Patient recruitment, hearing testing, baseline assessments, and follow-up evaluations will be conducted in the Department of Otorhinolaryngology at Peking University People’s Hospital. Acupuncture treatments on the study participants will be provided in the Acupuncture and Moxibustion Department of Beijing Traditional Chinese Medicine Hospital Affiliated with Capital Medical University. Both the participants and the acupuncturist will be aware of the treatment groups, but investigators performing assessments will be blinded. The acupuncture treatment will consist of 12 sessions over a period of 4 weeks. The participants will be assessed at baseline, post-treatment (week 4), and follow-up (week 28). This trial will be performed in accordance with the principles of the Declaration of Helsinki (Version Fortaleza 2013). The study protocol has been approved by the Research Ethics Committee of Beijing Traditional Chinese Medicine Hospital Affiliated with Capital Medical University (reference 2014BL-063-02). All participants will sign an informed consent form. The trial will be conducted from September 2018 to June 2020.

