### Outcome measures

Audiometry (pure tone hearing test), Word Recognition Score (WRS), and Tinnitus Handicap Inventory (THI) will be used to assess the participants before and after treatment (at weeks 4 and 28). The primary outcome measure will be the effectiveness of hearing improvement, defined as the proportion of patients with an improvement of at least 15 dB in their hearing loss frequency band [25]. For hearing improvement, complete recovery will be defined as hearing level equal to that of the unaffected ear or to hearing prior to ISSNHL [25]. Hearing gains of greater than 30 dB will be considered significant, gains of 15 to 30 dB will be considered effective, and gains of less than 15 dB will be considered ineffective [25]. The secondary outcome will measure the improvements in Pure Tone Average (PTA) (dB HL) [2], in WRS [2] and in THI [26].

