### Sample size

Sample size was calculated on the basis of a single-arm pilot study that showed an effective rate of hearing improvement in 33% of the acupuncture-plus-Methycobal group according to the Chinese sudden hearing loss multi-center clinical study group [19]. We assumed that the effective rate of hearing improvement in the group with only Methycobal was 5%. The difference of the effective rate between the two groups was 28%. This study will be based on 0.8 power to detect a significant difference (α = 0.05, two-sided). In this case, it means that 26 participants will be required for each group, as calculated using PASS 2008. To allow for a 15% withdrawal rate, we plan to enroll 31 participants per group, amounting to a total of 124 participants.

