### Statistical analyses

The de-identified outcome data will be analyzed by a statistician blinded to group allocations using the Statistical Package for the Social Sciences V.19.0 statistical software package (SPSS, Chicago, IL, USA). Significant levels will be set at a *P* value of less than 0.05. Data analysis of baseline characteristics and of primary and secondary outcomes will be based on the intention-to-treat principle. The chi-squared test will be conducted for proportions and independent samples. The *t* tests will be analyzed for testing the baseline differences between the two groups. A repeated-measures analysis of variance (ANOVA) will be used to compare the effect of the treatments between the two study groups. Any missing data will be replaced according to the principle of the last observation and carried forward.

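### Last observation carried forward is the only missing-data rule: it scores a missing week-4 audiogram as a failure, pulls week 28 toward week 4, and can bias the open-label comparison in either direction

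*Protocol article*

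**What the plan says.** The Statistical analyses section of the protocol article applies intention to treat to the primary and secondary outcomes and names one missing-data rule: "Any missing data will be replaced according to the principle of the last observation and carried forward". It names no other method.

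Three other parts of the article determine what that rule does:

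- **Visits.** Study design and Outcome measures give assessments at baseline, week 4 and week 28, with none between baseline and week 4.
- **Primary outcome.** Outcome measures defines it as "the proportion of patients with an improvement of at least 15 dB in their hearing loss frequency band", and adds that "gains of less than 15 dB will be considered ineffective".
- **Exposure to missing data.** Study design says "Both the participants and the acupuncturist will be aware of the treatment groups". The acupuncture groups have 12 sessions in 4 weeks; the control groups take oral Methycobal without them. Sample size raises the number per group from 26 to 31 "To allow for a 15% withdrawal rate".

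Long-term effect is a stated aim in the Abstract and the Background.

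**The concern.** With only one assessment between baseline and follow-up, the last observation for anyone without a week-4 audiogram is the baseline value. The gain is then 0 dB by construction and falls in the ineffective class. For week 4 the rule is baseline carried forward, although the protocol does not call it that.

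This matters because the arms differ in visit burden, in contact with staff and in what participants know. The Discussion defends the absence of a sham on the ground that the primary outcome is not subjective. That answers bias in measuring hearing. It does not answer bias from a value that was never measured.

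At week 28 the rule assumes that hearing has stayed where it was at week 4. Persistence of the effect is what the long-term aim is meant to test.

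**Working it through.** **Inputs from the protocol (Sample size).** Response 33% ("an effective rate of hearing improvement in 33% of the acupuncture-plus-Methycobal group") against an assumed 5% on Methycobal alone; two-sided α = 0.05; power 0.80; 26 evaluable and 31 enrolled per group; 124 in total.

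**The plan's own figure.** The unpooled normal formula gives (0.33×0.67 + 0.05×0.95) × (1.960 + 0.842)² / 0.28² = 26.9. Exact binomial power of the uncorrected chi-squared test at 26 per group is 80.2%, which matches the stated 26. Then 26/0.85 = 30.6, so 31, and 4 × 31 = 124. The sample size reproduces.

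**Assumptions added here.** Each missing participant lacks the week-4 audiogram and would otherwise have responded at the rate of his or her arm. The missing fractions are d_A (acupuncture) and d_C (control). Rejection rates come from exact enumeration of the uncorrected chi-squared test, with 31 per arm (one audiogram type) or 62 per arm (both types pooled).

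**Week 4, no true effect.** The rate under the rule is p(1 − d), so the false difference is p(d_C − d_A). With d_A = 5% and d_C = 25%:

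| Common rate p | False difference | Rejection favouring acupuncture, 31/arm | 62/arm |
|---|---|---|---|
| 33% | 0.33×0.20 = 6.6 points | 8.3% | 12.6% |
| 15% | 0.15×0.20 = 3.0 points | 5.8% | 6.9% |
| 5% | 0.05×0.20 = 1.0 point | 1.9% | 4.0% |

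The nominal value is 2.5%. A milder 10%/20% split at p = 33% gives 3.3 points and 4.7% at 31 per arm. A more extreme 0%/30% split gives 9.9 points, with 13.7% and 23.1%. Reversing the 5%/25% split at p = 33% reverses the sign, and rejection favouring acupuncture falls to 0.6% at 31 per arm.

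**Week 4, planned effect of 33% against 5%, 31 per arm.** The difference under the rule is 0.33(1 − d_A) − 0.05(1 − d_C).

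| Missing, acupuncture / control | Difference | Power |
|---|---|---|
| none | 28.0 points | 85.7% |
| 15% / 15% | 28.05 − 4.25 = 23.8 points | 78.7% |
| 25% / 5% | 24.75 − 4.75 = 20.0 points | 65.7% |
| 5% / 25% | 31.35 − 3.75 = 27.6 points | 88.2% |

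The 15% inflation treats withdrawals as removed, leaving 26 per group and 80.2% power. The analysis keeps them as failures, which gives 78.7%.

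**Week 28.** Assume a 28-point difference at week 4, a fraction m missing at week 28 but observed at week 4, and missingness unrelated to outcome. The estimate is (1 − m) × true week-28 difference + m × 28.

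- True difference 0: 0.15×28 = 4.2 points with 15% missing; 0.30×28 = 8.4 with 30% missing.
- True difference 14: 0.85×14 + 4.2 = 16.1 points; 0.70×14 + 8.4 = 18.2 points.

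**The case against.** **A false acupuncture effect should not be presumed.** A reader might infer that controls will leave more often and so manufacture a benefit. The documents do not support a direction. Controls receive no acupuncture, but acupuncture patients must attend 12 sessions at a second hospital, and the Discussion expects that controls would not look for acupuncture elsewhere. This objection stands: the bias can go either way.

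**At the protocol's own control rate the false difference is small.** The Background and Discussion expect little recovery after two weeks. If acupuncture does nothing, both arms may sit near 5%, where a 5%/25% split yields 1.0 point and 1.9% rejection at 31 per arm, below nominal. This also stands. A higher common rate cannot be excluded, however: the 33% comes from a single-arm pilot and the 5% is an assumption.

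**Not every withdrawal becomes a failure.** Someone who stops treatment but still has the week-4 audiogram is not imputed. The rule acts on missing audiograms, not on withdrawal as such.

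**The rule does not make long-term effects unobservable.** It changes only missing values; with 15% missing, 85% of week-28 data are still observed. It could supply the whole week-28 hearing result only if no audiograms were done then. Outcome measures lists audiometry at week 28, while Blinding has telephone interviewers collecting the follow-up material. Those sections need reconciling, but that is a separate matter.

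**Standard errors.** Treating imputed values as observed understates uncertainty for the continuous outcomes. For the binary week-4 outcome, missing-as-failure is a composite with ordinary binomial variance, so the point does not carry over.

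**Sensitivity analyses may be in an analysis plan not shown.** True, and their absence from the article is not held against it. The criticism is of the primary rule that the article does fix.

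**Conclusion.** The concern holds in a conditional form. The rule as written turns a missing week-4 audiogram into a failure and a missing week-28 value into the week-4 value (or baseline, if week 4 is also missing). With no true effect, it biases the week-4 comparison whenever missingness differs between arms, by p(d_C − d_A). With the planned effect, even equal 15% missingness shrinks the difference from 28 to 23.8 points, so balance does not make the rule neutral.

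Under the assumed 5%/25% split, the false difference runs from 1.0 point at a 5% common rate to 6.6 points at 33%. Under the reversed split, power for the planned effect is 65.7%. At week 28 the estimate moves toward week 4 by the missing fraction of the gap: 4.2 points at 15% missing and 8.4 at 30%, if a 28-point difference has vanished.

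The splits, the 15% and 33% common rates, and the week-28 scenarios are assumptions; the 5%, the 33% for the acupuncture group and the overall 15% withdrawal are the protocol's. The documents do not show that the result will favour acupuncture, nor that long-term effects cannot be assessed. This is a should-fix point.

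**What to change.** In Statistical analyses, drop last observation carried forward and state instead:

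1. **PTA, WRS and THI:** a likelihood-based mixed model on the observed values.
2. **Responder outcome:** multiple imputation of the dB gain, then classification at 15 dB. Use one imputation model containing arm, audiogram type, baseline threshold, time since onset and any observed gain. Do not fit separate models in cells of about 31: at a 5% rate, a control cell would hold only one or two responders (31 × 0.05 ≈ 1.6).
3. **Sensitivity analyses:** missing-as-failure, declared as such, and a tipping-point analysis that varies the assumed response among missing participants in both arms. These are needed because the imputation does not cover missingness that depends on recovery nobody measured.

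The cost is a change of wording and a little more analysis work. No visit, measurement or sample-size change is required.

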## Discussion

As many as two thirds of patients with ISSNHL may recover within 2 weeks [2, 9–11]; some do not achieve any additional recovery after this time [12, 13]. Current methods to treat ISSNHL are insufficient. In our previous research, we found that 30% to 40% of patients with ISSNHL experienced hearing improvement after acupuncture treatment. However, the beneficial effects of acupuncture treatment have not been verified through an RCT. This trial will be the first RCT of acupuncture based on audiometric curves. ISSNHL with low-frequency drop audiograms has the best prognosis after routine Western medical treatment [18]; the effective rate is more than 75% [20, 21]. Conversely, complete/profound deafness has a very poor prognosis [18]. ISSNHL with middle-frequency drop audiograms is rare [18]. The first 2 weeks after the onset of ISSNHL offer the best opportunity for recovery [2, 12]. Patients who do not show any improvement within the first 2 weeks are unlikely to have much recovery afterwards [6, 10]. It has been suggested that acupuncture can be used as a salvage therapy for ISSNHL within 4 weeks after the onset of the disease. However, prior studies examining acupuncture for ISSNHL have not sufficiently addressed the period from its onset. Therefore, we chose early ISSNHL patients with flat or high-frequency drop audiograms to evaluate the efficacy of acupuncture treatment.

The most common ISSNHL assessment parameter, the effective rate of hearing improvement, will be used in this trial as the primary outcome measure. We will assess changes in PTA, WRS, and THI as the secondary outcome measures. WRS is widely used to evaluate hearing because the most commonly reported complaint in patients with hearing loss is the inability to understand speech [27]. Furthermore, American guidelines recommend the use of WRS to assess the effectiveness of treatment [2]. THI is also used to assess treatment effectiveness because more than 70% of patients with ISSNHL have tinnitus, which can cause extreme anxiety and depression [2].

Generally accepted treatments for longer-term ISSNHL are still lacking. Even though some Western medicines have been suggested, the evidence of their efficacy is still unclear. This study aims to explore the efficacy of acupuncture treatment for patients with ISSNHL on top of Western medicine treatment. In this study, participants in the control group will receive Methycobal only, without sham acupuncture, because all patients in the control group will be recruited from a Western medical hospital which does not offer acupuncture treatment and this means that these patients would not seek acupuncture treatment. In some acupuncture research, sham acupuncture was used in order to decrease the bias of subjective quantity from patients, such as pain. In this study, the primary outcome measure will be focused on the effective rate of hearing improvement, as this is not a subjective measure, so sham acupuncture is unnecessary for this study.

This study will have its own limitations and some of them include that, for ethical reasons, there will not be a treatment group that receives acupuncture only. Second, neither the acupuncturist nor the patients will be blinded to treatment. It is almost impossible to have genuine double blinding in acupuncture trials because most participants in China have basic acupuncture knowledge and acupuncturists require patient feedback during the needling process. This article presents the design and protocol of an RCT of acupuncture as an early treatment and salvage therapy for ISSNHL. Completion of this trial will clarify the efficacy of acupuncture to treat ISSNHL patients with flat or high-frequency drop audiograms.

It is believed that acupuncture can treat ISSNHL and the possible basis for this belief might be that acupuncture can promote blood flow to the ear and decrease blood viscosity [28, 29]. Another study showed that acupuncture can improve blood circulation in the ear and increase the oxygen supply in the ear, all of which are important factors in promoting auditory recovery [30]. Other studies have found that acupuncture at acupoints around the ear may reduce blood viscosity, regulate the inflammatory response, improve lymph circulation, and enhance the excitability and conductivity of the auditory nerve [31, 32]. The exact mechanisms that explain acupuncture effects on ISSNHL have not yet been resolved; hence, further detailed research and discussion are needed in the future Additional file 1.

## Trial status

Recruitment will start in September 2018 and will be completed by the end of June 2020.

## Abbreviations

CRF: Case report form
dB HL: Decibels Hearing Level
ISSNHL: Idiopathic sudden sensorineural hearing loss
PTA: Pure Tone Average
RCT: Randomized controlled trial
TCM: Traditional Chinese medicine
THI: Tinnitus Handicap Inventory
WRS: Word Recognition Score
